#### 3.4 Secondary endpoints

The secondary endpoints are to determine/measure/assess:

- Haemoglobin concentrations over time:
  - Fractional change in haemoglobin on Day 7 vs. baseline
  - Proportion of patients with a fractional change  $\geq 25\%$
  - Time to nadir Hb concentration
- Determinants of changes in Hb concentration over time
- G6PD genotype (hemizygous male, homo-, heterozygous female, normal and selected G6PD variants e.g. G6PD A- 202 mutation)
- G6PD enzyme activity

- Genotypes of other inherited blood disorders
- Incidence of adverse events
- Pharmacokinetic characteristics of PQ, carboxyPQ, lumefantrine and piperaquine
- CYP 2D6 genotypes
- Asexual parasitaemia clearance time and half life
- Therapeutic efficacy of AL and DHAPP using the WHO criteria (Appendix 3)
- Gametocytaemia over time
- Proportion of patients with gametocytes over time

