### 3.10 Drug allocation and randomisation

The study has four dosing groups for the G6PDds and four dosing groups for the G6PD normals:

- AL + SLDPQ

- AL + SLDPQ placebo
- DHAPP + SLDPQ, and
- DHAPP + SLDPQ placebo.

A computer generated randomisation list will be generated for each site:

- one list for G6PDd patients and
- one list for G6PD normal patients.

The treatment allocation will be placed in a sealed opaque envelope which will be opened after a study (randomisation) number is given. The treatment allocation will describe the ACT to be given and the number of the PQ/placebo pack.

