## 11.2 Analyses & analysis populations

All patients who received at least one dose of ACT and PQ/placebo will be included in the analysis. All analyses will be detailed later in a prospectively written analysis plan. Below is a summary.

The main strategy for analysis of the primary end point will be assessed by chi squared or Fisher's exact test, as appropriate, calculating the 95% CIs of the risk difference to see if ACT + SLDPQ has achieved non-inferiority in the G6PDd group. Logistic regression will be used to adjust for potential confounders. Non inferiority will be assessed on the whole data set i.e. combining data from both sites using the lower end of the 95% confidence interval. Other proportional data will also be analysed by chi squared or Fisher's exact test.

Continuous data (e.g. Hb, biochemistry, parasite counts) between two groups will be analysed by the unpaired 't' test, transforming the data, as needed.

All analyses will be two sided and a p value of < 0.05 is considered statistically significant.

We will examine factors that are associated with: (i) the development of profound / severe anaemia (logistic regression), (ii) parameters of Hb recovery (multiple regression). *A priori*, we will explore the relationships between Hb profiles in the following: (i) G6PD status (defined by genotype and by enzyme activity), (ii) any IBD vs. not, (iii) age <5 vs. age ≥5y, (iv) high biomass infections, assessed by microscopy and measured HRP2 concentrations, and (v) males vs. females. For these analyses, estimates and 95% confidence intervals (CIs) will be presented but not p values.

The PK data for PQ and cPQ will be analysed by non-compartmental analysis. The following PK parameters will be estimated:

- Cmax
- Tmax
- Clearance
- Half life
- AUC
- Vd

For lumefantrine and piperaquine, drug absorption kinetics will be modelled over the first 24 hours.

The Day 7 concentrations of lumefantrine and piperaquine will be compared between PQ and placebo recipients. Depending on the lumefantrine and piperaquine data obtained, other modelled PK parameters will be determined, as the data permit.

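### The SLDPQ versus placebo comparison of Hb is planned as an unpaired t test without baseline Hb or site, which is valid but less precise than an adjusted analysis of the same data

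*Protocol*

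**What the plan says.** Protocol section 11.2 sets the method for continuous outcomes and lists Hb first: "Continuous data (e.g. Hb, biochemistry, parasite counts) between two groups will be analysed by the unpaired" t test, with transformation where needed. No covariate is attached to that comparison.

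Section 3.4 gives as the first Hb endpoint "Fractional change in haemoglobin on Day 7 vs. baseline". Section 3.8 has Hb measured at enrolment. On allocation, section 3.10 says "A computer generated randomisation list will be generated for each site", with separate lists for G6PD-deficient and G6PD-normal children. AL or DHAPP is randomised together with SLDPQ or placebo (section 3.2).

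For the primary endpoint, section 11.2 says "The main strategy for analysis of the primary end point will be assessed by chi squared or Fisher's exact test, as appropriate", with a 95% interval for the risk difference, and "Non inferiority will be assessed on the whole data set i.e. combining data from both sites". It adds that "Logistic regression will be used to adjust for potential confounders". It also plans multiple regression for factors associated with Hb recovery, and section 2.2 has an objective of modelling what determines Hb change. The section describes its own status: "All analyses will be detailed later in a prospectively written analysis plan. Below is a summary".

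**The concern.** The trial asks whether SLDPQ causes clinically important haemolysis. The primary endpoint is rare: at the assumed 1.5%, about 12 events are expected among 800 G6PD-deficient children. The Hb comparison between SLDPQ and placebo therefore carries much of the information on haemolysis.

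A child's Hb at enrolment can be expected to predict Hb a week later. A t test that omits it leaves that explained variation in the error term, so the interval is wider than it need be. A chance difference in baseline Hb between arms also stays in the point estimate. With 400 per arm and an assumed SD of 1.8 g/dL, the 95% range for such a difference is ±1.96 × 1.8 × √(2/400) = ±0.25 g/dL. Expressing the outcome as a fractional change uses baseline but does not fully remove this dependence.

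**Working it through.** **Inputs.** From section 11.1: event rate 1.5%, margin 2.5 points, two-sided alpha 0.05, power 80%, 374 per group, 800 G6PD-deficient children. From section 3.6: children with Hb below 6 g/dL are excluded. Assumed, because the Protocol does not give them: correlation ρ between baseline and Day 7 Hb (0.3 to 0.7), mean Hb 10 g/dL, SD 1.6 or 1.8 g/dL, and site-specific rates and means.

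**1. The plan's own figure.** n = 2p(1−p)(z₀.₉₇₅+z₀.₈)²/Δ² = 2 × 0.015 × 0.985 × (1.960+0.842)²/0.025² = 371.1, so 372 per group against 374 stated. It reproduces within rounding. It rests on an unadjusted comparison of proportions, so nothing below changes it.

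**2. Raw Day 7 Hb.** With equal SDs, variance under ANCOVA relative to a t test on Day 7 Hb is 1−ρ². For ρ = 0.3, 0.5 and 0.7, ANCOVA with 374 × (1−ρ²) = 341, 281 and 191 children per group matches the t test with 374. The t test with 374 per group has 80% power for (1.960+0.842) × √(2/374) = 0.205 SD. For the same difference ANCOVA has 84%, 90% and 98%.

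**3. Change from baseline.** For absolute change with equal SDs, the correlation with baseline is −√((1−ρ)/2), that is −0.59, −0.50 and −0.39 for ρ = 0.3, 0.5 and 0.7. Adjusting for baseline then leaves (1+ρ)/2 = 0.65, 0.75 and 0.85 of the variance. Fractional change was simulated with normal Hb, dropping baselines below 6 g/dL. Its correlation with baseline was negative throughout, from about −0.3 to −0.6.

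Share of the t-test variance left after adjusting for baseline (ranges cover SD 1.6 and 1.8):

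| ρ | Raw Day 7 Hb, 1−ρ² | Fractional change, mean Hb steady | Fractional change, mean fall 0.5 g/dL |
|---|---|---|---|
| 0.3 | 0.91 | 0.66–0.67 | 0.69–0.70 |
| 0.5 | 0.75 | 0.76–0.77 | 0.79–0.80 |
| 0.6 | 0.64 | 0.80–0.81 | 0.84–0.85 |
| 0.7 | 0.51 | 0.85–0.86 | 0.89–0.90 |

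The two outcomes behave in opposite ways. A stronger correlation raises the gain over raw Day 7 Hb and lowers the gain over fractional change, but there is a gain in every row.

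**4. Site.** With equal numbers per site and site mean Hb d SDs apart, removing site leaves 1/(1+d²/4) of the variance: 0.985, 0.941 and 0.80 for d = 0.25, 0.5 and 1.0. Part of this would already be captured by baseline Hb.

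**5. Primary endpoint.** Expected events are 400 × 0.015 = 6 per arm. Total variance per child is 0.015 × 0.985 = 0.014775. With site rates of 1% and 2%, the within-site variance is (0.01 × 0.99 + 0.02 × 0.98)/2 = 0.01475, a ratio of 0.998. With 0% and 3% it is (0.03 × 0.97)/2 = 0.01455, a ratio of 0.985. Power moves from 80.3% to between 80.4% and 80.9%. Assumed spreads over the four site-by-ACT cells leave 0.992 to 0.996.

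**The case against.** Section 11.2 is openly a summary of a later analysis plan, and lists of covariates normally belong there. That stands for the detail of a model. It does not dispose of the point, because the section names a specific test for Hb and a later plan would have to replace that test, not just fill it in.

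Baseline is not ignored outright. The Day 7 endpoint is a fractional change, and regressions of Hb are planned. This also stands, and it limits the point. What is missing is baseline as a covariate in the comparison of SLDPQ with placebo. The planned regressions are described as looking for factors associated with recovery or determinants of change, not as that comparison.

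The unpaired t test is valid under randomisation, its interval already reflects chance imbalance, and Hb carries no margin or decision rule. All true: the loss is of precision only, on secondary outcomes. The larger figure, for raw Day 7 Hb, is also the less relevant one, since the named Day 7 endpoint is fractional change.

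A reader might infer that the primary analysis has the same fault, as a crude pooled table that wastes precision with an odds ratio set against a 2.5-point margin. The Protocol does not support this. The margin is judged on the interval for the risk difference, logistic adjustment is additional, and pooling the sites means that non-inferiority is not judged site by site. Stratifying by site would remove at most about 1.5% of the variance under the site rates assumed above. ACT is a randomised factor, not a stratum of the lists.

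**Conclusion.** The point holds for the Hb treatment comparison only. As written, it omits baseline Hb and site, and an adjusted analysis would be more precise with the same children and samples. For fractional change the gain is about 15 to 25% of the variance at assumed correlations of 0.5 to 0.7 with steady mean Hb. Over correlations of 0.3 to 0.7 and a mean fall of 0 or 0.5 g/dL it is about 10 to 35%. For raw Day 7 Hb it is about 25 to 50% at 0.5 to 0.7, and 9% at 0.3. These sizes rest on assumed correlation, mean and SD; the direction was the same in every case tried.

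The sample size, the validity of the t test and the non-inferiority conclusion are untouched. This is a modest improvement to secondary safety outcomes.

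**What to change.** In section 11.2, take the SLDPQ versus placebo comparison of Hb out of the general t-test sentence. State that it will be made within each G6PD stratum by ANCOVA, or by a mixed model over the scheduled days with arm-by-day terms, with baseline Hb, site and randomised ACT as covariates. For fractional change, analyse log Hb with log baseline Hb as a covariate, so that the Day 7 contrast back-transforms to a ratio of Hb between arms. The unadjusted comparison can be kept as supportive.

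For the primary endpoint, keep the risk difference and its interval. A site-stratified risk difference may be added as a sensitivity analysis in line with the per-site lists, without expecting a gain in precision.

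The cost is analysis wording only, with no extra patient, sample or visit. The change should be made before treatment codes are broken.

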### 2.2 Secondary Objectives

These are to:

- explore risk factors for developing profound or severe anaemia in this trial
- model the determinants of changes in haemoglobin concentrations over time
- characterise G6PD deficiency, other inherited blood disorders (IBDs) and the cytochrome 2D6 polymorphisms
- define the PK characteristics of PQ, cPQ, lumefantrine and piperaquine
- determine changes in gametocyte carriage over time
- measure the parasite clearance over time and the D42 cure rate

- assess the test characteristics of a G6PD Biosensor

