#### 7.1.2 Reading malaria blood films

Blood films will be prepared at baseline, 6 and 12 hours and then every 12 hours until 2 consecutive negative blood films are observed (inpatients only).

Asexual and sexual parasites will be identified and counted by microscopy (magnification of 1000×) on Giemsa-stained thin and thick films.

Parasitaemia will be measured on a thin blood film if more than 200 parasites per 10 fields on a thick film are seen: 2000 RBCs will be read and the number of parasitised infected RBCs noted.

Below this threshold, the parasitaemia will be counted per 500 WBC on the thick film.

Slides are considered negative after examination of at least 200 high-power microscopy fields.

The final parasitaemia is calculated as follows:

- Thin film:  $N \text{ parasites} / 2000 \text{ red blood cell on the thin smear} \times \text{Hct} \times 125.6$

2

- Thick film: N parasites/500 white blood cells on the thick smear x 16

Slides will be cross checked blinded by the research team, as follows:

- 10% of all D0 slides
- all positive slides on D3 and D7
- 10% of negative slides on D3 to D28.

Two qualified microscopists will read all the slides independently. Blood smears with discordant results:

- different parasite species
- a difference in parasite density of > 50%
- positive/negative slide

will be re-examined by a third, independent microscopist, and parasite density will be calculated by averaging the two closest counts.

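### Gametocyte density falls under an unadjusted t test with an open transformation, which fits a zero-heavy count poorly and leaves the Day 0 count unused

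*Protocol*

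**What the plan says.** Section 11.2 assigns a test by type of data: "Continuous data (e.g. Hb, biochemistry, parasite counts) between two groups will be analysed by the unpaired 't' test, transforming the data, as needed". It names no transformation and no baseline covariate for this comparison.

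Gametocyte counts come within that sentence. Section 7.1.2 says "Asexual and sexual parasites will be identified and counted by microscopy", and section 3.4 lists "Gametocytaemia over time" as a secondary endpoint. The film count moves in steps: "Thick film: N parasites/500 white blood cells on the thick smear x 16". A film can also be read as negative: "Slides are considered negative after examination of at least 200 high-power microscopy fields".

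Carriage is a separate endpoint in section 3.4, "Proportion of patients with gametocytes over time", and matches the objective in section 2.2 to "determine changes in gametocyte carriage over time". Section 11.2 covers it with "Other proportional data will also be analysed by chi squared or Fisher's exact test".

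Section 11.2 describes itself as a summary, to be followed by a detailed analysis plan.

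**The concern.** A t test on transformed data suits a roughly continuous outcome. Gametocyte density by film is a count with a step of 16 and probably many zeros, because entry does not require gametocytes.

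The open transformation leaves three obvious versions of the planned test:

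- **Log of positives only.** The log of zero does not exist, so children who have cleared drop out. Who remains depends on treatment: primaquine clears the low-density carriers first, and those left in the SLDPQ arm tend to have started high. The ratio is pulled towards 1.
- **No transformation.** Zeros stay in, but a few very high counts dominate the means and their variance.
- **log(x+c).** Zeros stay in and power is reasonable, but the estimated ratio changes with an arbitrary constant.

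None of them uses the Day 0 gametocyte count, which is collected anyway and should predict later density strongly. Density and carriage are where the trial measures the drug's intended effect, so a diluted or constant-dependent density ratio would be a poor result to report, even from a secondary endpoint.

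**Working it through.** The protocol states no power, carriage or density figure for gametocytes, so there is no planned figure to reproduce. The size of the problem has to come from simulation.

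**Inputs from the protocol**
- Two-sided 5% test (11.2).
- 1,600 children (11.1), half allocated to SLDPQ: 1,600 / 2 = 800 per arm, pooling both ACTs and both G6PD strata.
- Film step: 1 parasite per 500 white cells × 16 = 16 (7.1.2), taken as per µL.

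**Assumed inputs**
- 25% carriage at Day 0; median density 50/µL in carriers; SD of log density 1.6.
- Gametocyte half-life 4 days on placebo, and 2 days (strong effect) or 3 days (weaker effect) on SLDPQ; SD of log half-life between children 0.4.
- Day 7 count = Poisson(density / 16) × 16.

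**True effect.** The fraction left at Day 7 is 2^(-7/h). Without variation between children, the ratio for 2 against 4 days is 2^(-3.5) / 2^(-1.75) = 2^(-1.75) = 0.30. For 3 against 4 days it is 2^(-2.33) / 2^(-1.75) = 2^(-0.58) = 0.67. With half-lives varying between children, the ratios of mean density become 0.36 and 0.72.

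**Results at Day 7** (repeat runs agree within a few points)

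| Analysis | Power, 4 vs 2 d | Power, 4 vs 3 d |
|---|---|---|
| Log t test, positives only | 60% | 14% |
| Raw t test | 78% | 17% |
| log(x+1) t test | 99% | 26% |
| Log-link count model, no Day 0 covariate | 84% | 25% |
| Zero-keeping models with Day 0 density | 100% | 66-75% |
| Chi squared on carriage | 94% | 21% |

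**Estimates.** The positives-only geometric mean ratio is 0.73 against a true 0.36, and 0.89 against a true 0.72. For the strong effect, log(x+c) gives 0.69 with c = 0.1, 0.78 with c = 1 and 0.90 with c = 16. It is attenuated each time, by an amount set by the constant.

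**Where the gain arises (weaker effect).** Keeping the zeros moves power from 14% to 26% with log(x+1), a gain of 12 points. Adding Day 0 density moves it from 25-26% to 66-75%, a further 66 − 26 = 40 to 75 − 25 = 50 points. Most of the gain is the covariate.

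**Sensitivity to carriage.** For the strong effect with 15-35% carriage, positives-only power is 38-73%, log(x+1) 89% to about 100%, and the carriage test 80-99%.

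**A drug that acts on carriage alone.** In a second set of assumed settings (20% vs 5% carriage with 100 or 400 per arm; 40% vs 10% with 100 per arm; same density in carriers), the positives-only log t test has 4-5% power, the nominal alpha, and a ratio near 1. The raw t test has 37-73%, log(x+1) 89-100%, and chi squared on carriage 93-100%.

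**The case against.** A reader might infer that most children have zero counts, that log-transforming will drop them, and that much of the primaquine effect will be hidden. The protocol does not support that reading. It gives no zero fraction, names no log and says nothing about dropping zeros. Its population sentence includes all children who received at least one dose of ACT and of PQ/placebo. A log(x+1) t test fits the wording and has 99% power for the strong effect. Carriage is tested separately with non-carriers included, at 94% power in the same scenario, and the objective itself is worded as carriage.

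Two further objections stand. The advantage of the count model comes mainly from the covariate: without it the model has 84% and 25% power, no better than log(x+1). And the molecular assay in section 7.1.3 should leave fewer zeros, so the gap narrows, although that assay is planned only for a subset.

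The remaining objection is that transformation, zeros and covariates belong in the analysis plan, which is not at hand. That is true of detail left open, and nothing is faulted here as missing. But section 11.2 does name a test, the unadjusted t test, for a class of data that includes gametocyte counts. That stated choice fits poorly. Nor does log(x+1) settle the matter: its ratio depends on the constant, and its power for the weaker effect is 26%.

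**Conclusion.** The point holds as one of efficiency and estimation for a secondary endpoint. The named test fits gametocyte density poorly if zeros are common, and it ignores a baseline count that the trial collects. Under the assumed inputs, power for a weaker effect is about 14-26% with the t-test versions against about 66-75% with a baseline-adjusted analysis that keeps the zeros. The positives-only ratio is 0.73 where the true ratio is 0.36.

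The primaquine signal is not lost: for a strong clearance effect, both the carriage test and a log(x+1) t test would find it. For the weaker effect the carriage test has only 21% power, so there the density analysis matters more.

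All carriage, density and half-life values are assumptions. The power figures also assume both ACTs and both G6PD strata are pooled and films are used. The primary safety analysis is unaffected.

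**What to change.** In section 11.2, take gametocyte density out of the t-test sentence. Compare the arms on all children, zeros kept, with Day 0 gametocyte density as covariate. A log-link count model (quasi-Poisson or negative binomial) with robust standard errors would do, reporting the SLDPQ/placebo ratio of mean density at each visit with its 95% CI. Show density among carriers only as description. Leave the carriage test as it is. Fix the choice before unblinding, so that no transformation is picked after seeing the data.

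The cost is a wording change and a little more analysis work; no new data are needed, because Day 0 films are already scheduled. Robust standard errors were slightly liberal in simulation (null rejection about 7%), which flatters the upper end of the 66-75% range, so a small-sample correction is sensible. The gain does not depend on them: a linear model on log(x+1) with the Day 0 covariate gave 68% power for the weaker effect, though its ratio still depends on the constant.

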## **12 ETHICS**

### **12.1 Informed Consent**

All caregivers/legal guardians of all patients must give informed consent before they can enter the study. They will be given a patient information sheet (PIS) to read and a member of the research team will give a verbal explanation.

The PIS will detail the nature of the study, follow up schedule, the known side effects of AL, DHAPP and PQ and any other risks involved in taking part in the study and the total blood volume. It will be clearly stated that the caregivers'/legal guardian's decision to allow her/his child to join this study is voluntary and if she/he declines, this will not have any adverse consequences for future treatment at the hospital or clinic.

Caregivers/legal guardians will be allowed as much time as they need to consider the information and will have the opportunity to question the site Principal Investigator/research team doctors or other independent parties to decide whether they will participate in the study.

Written Informed Consent will then be obtained by means of subject dated signature, and the signature of the research physician who obtained the consent. If the caregiver/legal guardian cannot read or write, a thumb print is acceptable. In this scenario, an independent witness must sign the consent form as well. A copy of the signed Informed Consent will be given to the subject. The original signed form will be retained at the study site.

In Uganda at Mbale, the PIS and consent form will be in English and several local languages:

- Luganda
- Lugwere
- Ateso
- Swahili
- Lumasaba

If another site is used e.g. at Soroti, the Ateso and Kumam languages will be used. In Kinshasa, the PIS will be in French and Lingala.

The PIS/ICFs for Uganda and Kinshasa have been prepared in accordance with the specific requirements of the local ethics committees and are version controlled for each country.

